## Methodology

The study design is an impact evaluation based on a quasi-experimental design (QED), with integrated implementation and process (IPE) and economic (EE) evaluations. These are situated within a theory-based approach and a commitment to co-production, which will guide all aspects of the study. Theory-based approaches [59] are optimal for evaluating complex social interventions. We are aiming to understand whether BIP changes specific outcomes, how it may have these effects, why and for whom it may be beneficial or detrimental, and under what conditions these changes may happen [60]. Logic models that delineate the mechanisms that underpin the anticipated effects of BIP, and of basic income schemes more broadly, provide a basis for ‘theory enhancement’ using data from this evaluation. An updated programme theory and logic model will therefore be a key output.

Co-production is increasingly recognised as essential to high quality research and policy practice and is in keeping with Welsh legislation and policy, including the Social Services and Well-being Act 2014. Co-production will underpin the study and our participatory methods encompass the entire research cycle, and follow the UK Standards for Public Involvement in Research (NIHR) [61] and Wales’s Participation Standards [62]. A group of care-experienced young adults, living in a range of educational, employment and housing situations, will meet for a minimum of 16 sessions to advise the research team. Their role is to co-create research questions, data collection instruments, consider ethical and analytical questions and advise on policy and practice implications.

### Impact evaluation

To measure impact the design incorporates a suite of quasi-experimental designs (QEDs) which will enable triangulation between multiple data sources and provide a robust account of the difference the BIP makes to care leavers in Wales. QEDs attempt, in the absence of randomisation, to achieve identification of the causal impact of one or more interventions, primarily through a mix of sample selection and statistical approaches [63]. Randomisation is not possible in this case because the BIP is open to all eligible young people and starts at the same point for all participants (the month after their 18^th^ birthday). The QED approach will enable us to determine that, conditional on our sample selection and analytical strategy, we do not expect to see any uncontrolled-for differences between the intervention and counterfactual groups, and so any differences between the two groups can be attributed to the BIP. Further detail about our analysis plan is available in supplementary materials.

We aim to compare the outcomes of care leavers who turn 18 during the enrolment year (and are thereby eligible for the BIP), to outcomes of care leavers in Wales who turn 18 the following year. This will involve two quasi-experimental approaches: coarsened exact Matching (CEM) and difference in differences (DID). Measurement will take place at two time points. Baseline data will be gathered around the individual’s 18^th^ birthday (referred to below as time t-1) and follow-up data will be gathered around their 20^th^ birthday (referred to below as time t).

#### Outcomes and data sources

The Welsh Government identified six outcome domains of interest, and the literature suggests that it is also important to include physical and mental health outcomes more broadly. These, and the means of collection through surveys and administrative records, described below, are outlined in Table 1.

**Table 1 pone.0303837.t001:** Outcomes and data sources.

Outcome domain	Collected through	Specific measures
Wellbeing/ psychological Wellbeing	Survey Data	Categorical indicators of frequency of emotional states, level of anxiety, happiness, feelings of positivity, including an open-ended question
Financial literacy/ security	Survey Data	Questions on levels of financial coping, allocation of income, spending habits with an open-ended question on money management.
Community cohesion/ engagement	Survey Data	Binary indicators of friendship, partnership, owning a pet, having a person of trust, and categorical indicators of emotional support. Binary indicators of community cohesion in follow up (t) survey
Ameliorating the effects of poverty	Survey and administrative data	Categorical indicator of current housing, binary indicator of housing satisfaction Leisure and access to luxury items/internet
Access to labour market/ education/ lifelong learning	Administrative data	Binary indicator of employment; continuous measure of earnings; binary indicator of enrollment in education or training; binary indicator of participation in higher education; binary indicator of participation in further education. These outcomes will be extended using linked longer-term data from the Longitudinal Education Outcomes (LEO) data.
Volunteering and life skills	Survey Data	Education, employment and training.
Physical and mental health	Survey and administrative data	Self-rated general health (ONS question) Limiting long-term illness (ONS question) Common mental disorders: depression (PHQ-2); anxiety (GAD-2).

The Welsh Government have not specified what effect they expect BIP to have on these outcomes, though they aim for the policy to empower participants, give them more agency and control, and improve their lives. The literature on basic income suggests that we should not see any detrimental effects in any of these areas, and that in many areas improvements would be hypothesised. Some of these improvements may take longer than others to materialise, meaning that some benefits may not be detectable during the timescale of the study. This study will publish analysis of the observed effects on all outcomes in Table 1. The measures cited were selected by the evaluation team and approved by the Welsh Government.

*Survey data*. We are contracted to use data already collected by Coram Voice, who are a third-party commissioned earlier by the funder to gather survey data from participants of the BIP. Surveys will be administered by Coram Voice for the intervention group and comparator group at two time points (t-1; around the participants 18^th^ birthday, t; around the participants 20^th^ birthday). It should be noted that both of these time periods differ for each participant in the study, because they turn 18 at different points during the enrolment window. Therefore data collection will, in practice, take place continuously over the study period.

The survey is based on a similar survey used with care leavers extensively in England, called ‘Your Life Beyond Care’ [6]. Coram Voice started collecting data in Wales in October 2022, 4 months after the pilot had started, and initially included only the original questions used in the ‘Your Life Beyond Care’ survey. In January 2023 an updated survey was released with additional questions designed to cover the broader range of outcomes in Table 1. The new questions added were the result of negotiations between the evaluation team, the funder, and Coram Voice. At the point we were commissioned, in November 2022, survey response rates for the original survey were 6%. After several changes to the mechanism for collecting survey data were agreed, and questions added, response rates increased and the final response rate is 64%. The Welsh Government and Coram Voice take informed consent for survey data.

*Administrative data*. We will use the Longitudinal Educational Outcomes (LEO) dataset which is held by the Office for National Statistics (ONS) and the Welsh Government. This resourcelinks educational data from the National Pupil Database (NPD) for England, the Pupil Level Annual School Census (PLASC), the post-16 pupil collection and the Lifelong Learning Wales Record for Wales, employment and earnings data from HM Revenue and Customs (HMRC) and the Department for Work and Pensions (DWP), progression and success in further education from the Individualised Learner Record (DfE) and progression to higher education from the Higher Education Statistics Agency. LEO also contains markers for young people’s social care experience, which will allow us to identify care leavers in both England and Wales. We will initially consider the universe of data on care leavers from England and Wales, and will use a two stage matching process (detailed below and in more detail in our Statistical Analysis Plan), to select a group of English care leavers who are (a) in English local authorities that are comparable to the 22 Welsh local authorities and (b) who are comparable to the Welsh care leavers within those local authorities.

Use of administrative data will allow us to link the intervention group with a large enough comparable group of young people experienced in care during the same period in which the intervention took place. This will provide the analysis with higher power, increasing precision while allowing for a broader range of outcomes to be explored. Administrative data will also allow for a contemporaneous comparison of outcomes between the control and the intervention. This will enhance causal inference with respect to unobserved time-dependent covariates that may have been correlated with the outcome(s) of interest at the time of the intervention, an aspect of analysis which is not possible in the survey-based analysis.

Outcomes within administrative data will be aligned with various outcomes already explored within the survey (see Table 1), thus allowing for accurate inference on the effect of the intervention. For outcomes not covered by the survey, a binary interaction indicator of whether the participant was in a local authority that would make them eligible for the basic income payments at the time of the intervention will be used to capture the treatment effect.

Other administrative data will also be available from the Welsh Government. They are managing the enrolment of eligible young people in collaboration with the 22 local authorities. Each participant completes an enrolment form at the outset, and this includes a tick box for consent to be included in the evaluation. Enrolment forms contain a range of monitoring data, including some self-reported data about the individual’s health circumstances. The Welsh Government are designing an exit process that may mirror aspects of enrolment, but are yet to finalise this at the time of writing. Some data items gathered at the enrolment stage for participants in the intervention group will be added to surveys completed by participants in the comparison group (as these data would otherwise be missing for this group). The Welsh Government will take informed consent for monitoring data to be shared with the evaluation team.

*Sample size*. In the evaluation specification, the Welsh Government advised that around 550 young people were expected to become eligible for the intervention during the enrolment period. (The actual update for the scheme is 635 recipients.) Power calculations are difficult to usefully conduct ex ante for a matched difference-in-differences approach, reflecting the relative complexity compared with the canonical RCT approach. Nonetheless, we anticipate being able to detect effects on survey outcomes of no more than 0.2 standard deviations (calculated via Glass’s Delta), and for effects of no more than 0.12 standard deviations for the administrative data, based on our experience with other similar projects. These effect sizes are comfortably within the range of small effects, allowing us to build a clear picture of the impacts of basic income. However, it should be noted that the small sample size makes subgroup analysis, particularly for any group which is in a minority among eligible participants, difficult to conduct reliably.

*Matching procedure*. Coarsened Exact Matching (CEM) [64] lies somewhere between the two extreme forms of matching - the completely uncoarsened Exact Matching, or the logical extreme of coarsening to a single figure - the Propensity Score [65]. In CEM, matching variables are preserved, but are coarsened. Here, we can think of coarsening as redefining variables into ranges. For example, instead of a participants’ height being an exact number of centimetres, which might be difficult to match in small samples, this could be coarsened to heights in ten centimetres intervals. By doing this, participants continue to be matched on the values of their observable characteristics, but the likelihood of matching on any variable or set of variables is increased.

This matching approach has the advantage of yielding more matches than exact matching, while also ensuring that units are matched on measures that are relevant to the *outcomes* of interest.

For the administrative data, we will use Coarsened Exact Matching at two levels - first to match Welsh local authorities with their English counterparts, effectively matching treated local authorities to statistically *similar* untreated authorities, and second to match care leavers within those local authorities with each other. To identify counterfactual local authorities in England we accessed publicly available information on the age, legal basis, gender, and numbers of care leavers in local authorities in England and Wales from 2018-2022, and merged these into a single dataset with a panel at local authority/year level. This panel was then used to identify variables capturing the rate of change in the children in care within each local authority in England and Wales.

We further accessed data on indices of multiple deprivation for England and Wales, particularly focusing on the indices employment, income and childhood deprivation at MSOA level, which was subsequently collapsed to give a local authority level average for each score for all top tier local authorities in England and Wales (which deliver children’s services). This was in turn matched into the panel dataset created previously.

When matching using Income Scores, IDACI score and IDAOPI score, we identified 41 matches for 21 Welsh local authorities. Using Employment Score instead of IDAOPI score produced 29 matches for 18 Welsh Authorities. Reducing this to only Income scores and IDACI Scores yielded 71 matches for all 22 Welsh local authorities. Given the need for some specificity of matches (more than half the local authorities available for matching are matched in the second model) the first or second approach, which only identifies matches for 21/18 Welsh local authorities are preferred at this stage.

For both of our potential models, we test balance on trends in care numbers, and any omitted scores. We find that our second model, which includes Employment rather than IDAOPI, creates a more balanced sample overall, except for with respect to IDAOPI, which is significantly imbalanced.

For survey data, we will match at care leaver level, matching care leavers in the treatment cohort with statistical neighbours in the subsequent cohort (both cohorts being in Wales). Where possible this will involve matching participants on a range of variables *including* their local authority. Matching for survey data can therefore not take place until after data is collected.

*Difference in differences*. Difference in Differences approaches are quasi-experimental approaches which compare the differences between treated and counterfactual units, before and after the introduction of a new policy or intervention (Fig 1 below). This comparison allows for time invariant differences, whether observed or unobserved to be controlled for analytically [66]. We will undertake two different versions of the difference in difference approach for our two separate data sources. For administrative data, we will make use of a standard difference in difference in which participants in Wales are compared with matched English care leavers, covering the same time period (and same life stage) as the Welsh Data. For our survey outcomes, due to the challenges associated with collecting data from English care leavers, we will instead draw our counterfactual group from the subsequent cohort of Welsh care leavers. Although the comparison of two groups that have not been measured contemporaneously (as is the case comparing Welsh Care leavers in one cohort with Welsh Care leavers in another) is a non-standard implementation of the difference in differences methodology, the underlying assumptions remain the same. Instead of assuming common trends in the macroeconomic conditions (as would be the case for a standard DID), we are instead assuming common trends over the same period of the life course – that is, we assume that outcomes change in the same ways for young people between their 18^th^ and 20^th^ birthday, for young people whose 18^th^ birthdays were up to a year apart. The broad approach to a Difference in Differences approach can be seen in Fig 2.

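### The two candidate sets of matched authorities are compared by balance tests with significance as the only stated criterion; with 62 or 47 authorities, non-significance says little about balance

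*Protocol article*

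**What the plan says.** The Matching procedure text of the protocol article describes coarsened exact matching at two levels for the administrative data, first of authorities and then of care leavers within them. Three sets of authority-level matching variables were tried:

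- Income, IDACI and IDAOPI scores: "we identified 41 matches for 21 Welsh local authorities".
- Employment in place of IDAOPI: "Using Employment Score instead of IDAOPI score produced 29 matches for 18 Welsh Authorities".
- Income and IDACI only: this "yielded 71 matches for all 22 Welsh local authorities".

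The third is set aside because its matches are not specific enough, and "the first or second approach, which only identifies matches for 21/18 Welsh local authorities are preferred at this stage". The article then reports a check on the two remaining models: "For both of our potential models, we test balance on trends in care numbers, and any omitted scores". The result is that the second model "creates a more balanced sample overall, except for with respect to IDAOPI, which is significantly imbalanced". No test statistic, significance level, standardised difference or acceptance limit is given.

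Under Primary analysis - administrative data, the regression includes a vector Q_l of authority-level characteristics, among them the matching variables. It enters additively and is not interacted with the treatment period.

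**The concern.** A significance test mixes the size of an imbalance with the number of units. Balance is a property of the matched sample in hand, so what matters is how large the remaining differences are. With few authorities, sizeable differences can be non-significant. When two match sets differ in size, the same difference is also less likely to be flagged in the smaller one.

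The choice between the two sets is still open, and it fixes which English authorities form the comparator for the administrative analysis. Differences in pre-period care trends matter most, because difference in differences removes stable level differences but not differential trends, and these trends are among the variables checked by testing. The article expects to detect effects of no more than 0.12 SD in the administrative data. That is an individual-level outcome scale and cannot be set directly against an authority-level covariate difference, but it shows that a fairly small bias would count.

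**Working it through.** The article gives no figure for the sensitivity of its balance tests, so there is nothing to reproduce.

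**Inputs from the article.** Model 1: 21 Welsh authorities and 41 matches, 21 + 41 = 62. Model 2: 18 Welsh authorities and 29 matches, 18 + 29 = 47.

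**Assumptions not in the article.** Two-sided 5% level; matches are distinct English authorities; unweighted comparison of two means; one row per authority.

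**Smallest significant standardised difference** = 1.96 × √(1/n₁ + 1/n₂).

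- Model 1: √(1/21 + 1/41) = 0.268; 1.96 × 0.268 = 0.53 SD.
- Model 2: √(1/18 + 1/29) = 0.300; 1.96 × 0.300 = 0.59 SD.

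With t quantiles (60 and 45 degrees of freedom) the values are 0.54 and 0.60 SD.

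**Range under other assumptions**

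| Assumption changed | Model 1 | Model 2 |
|---|---|---|
| 10% level (t) | 0.45 | 0.50 |
| 1% level (t) | 0.71 | 0.81 |
| Matches count both countries (21 v 20; 18 v 11), 5%, t | 0.63 | 0.79 |
| Five authority-years treated as independent (105 v 205; 90 v 145), 5%, normal | 0.24 | 0.26 |

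The last row is included because the article "merged these into a single dataset with a panel at local authority/year level". It says that the panel was used to derive rate-of-change variables, and repeated rows from one authority are not independent, so this row overstates the information available.

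**How often an imbalance would be missed** (non-central t, 5% level, one row per authority): a true imbalance of 0.5 SD would be non-significant 55% of the time in model 1 and 63% in model 2. For 0.25 SD the figures are 85% and 87%.

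**Effect of sample size on the comparison.** The ratio of standard errors is 0.300/0.268 = 1.12. An observed difference of 0.55 SD, chosen for illustration, gives z = 0.55/0.268 = 2.05 in model 1 and 0.55/0.300 = 1.83 in model 2. Size alone changes the result only between 0.53 and 0.59 SD, a window of about 0.06 SD.

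**Would a fixed limit on standardised differences work better as a pass/fail rule?** For a variable with no true imbalance and unrelated to the matching variables, the chance of an observed difference above 0.1 SD is P(|Z| > 0.1/0.268) = 71% in model 1 and P(|Z| > 0.1/0.300) = 74% in model 2. Above 0.25 SD it is about 35% and 41%. A rigid 0.1 SD rule would therefore often fail both sets by chance.

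**The case against.** The article refers readers to a statistical analysis plan for detail on matching, and that plan may hold the balance tables. Calling one sample more balanced overall is comparative wording that could rest on unreported magnitudes. This stands as a caution about what else exists. It does not remove the point, because the article reports a completed check and its conclusion, and significance is the only criterion it states.

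A reader might go further and infer that the smaller sample has been favoured because its tests had less power, or that imbalances above half a standard deviation have passed as balanced. The article supports neither. It keeps both models open, and it rejects the third for lack of specificity, before balance is mentioned. It reports no non-significant difference of any size. The 0.06 SD window is narrow, and nothing shows that any variable lay in it. The one imbalance called significant is in the smaller sample, and the authors disclose it.

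The consequences are also limited. Care leavers are matched individually in a second stage, difference in differences removes stable level differences, and Q_l adjusts for authority characteristics. This reduces the weight of imbalance in deprivation levels. It does not deal with differential trends, because Q_l has no interaction with period. Nor does the wording for Q_l guarantee that IDAOPI is included under model 2, where it is not a matching variable, although it does not exclude it either.

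**Conclusion.** The point holds as one of method, and it is minor. The article compares its two candidate authority sets by tests, with significance as the only stated criterion. Under a two-sided 5% test with one unweighted row per authority and distinct English authorities, differences up to about 0.53 SD (model 1) or 0.59 SD (model 2) would be non-significant. The half-SD order of magnitude depends on those assumptions: it is 0.45 to 0.50 SD at the 10% level and about 0.25 SD if authority-years were treated as independent. Non-significance is therefore weak evidence of balance, and the two sets have not been compared like for like. The sample-size effect between them is modest. It is not shown to have produced the reported result, and no choice of model yet rests on it.

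**What to change.** - Before choosing between the models, tabulate standardised mean differences and variance ratios for care-number trends, the deprivation scores and any omitted scores under each candidate model.
- Base the choice on those magnitudes, giving priority to pre-period trends. State any limit beforehand and treat it as a guide; a rigid 0.1 SD cut-off is not workable with this few authorities.
- If model 2 is used, name IDAOPI explicitly in Q_l. As Q_l is specified, this adjusts for level and not for differential trend, which is why the trend variables should lead the choice.

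The data are already assembled, so the cost is a little more analysis work and one or a few extra authority-level covariates. With 47 to 62 authorities those covariates use some degrees of freedom, so they should be kept few.
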